**11. Statistical design**

**11.1 Experimental design**

**It is a therapeutic trial of equivalence, with two parallel groups of which the main criterion is the rate of clinical cure at the end of treatment (D21).**

**11.2 Number of patients**

The calculation of the number of patients was carried out under the following conditions: the equivalence is accepted up to a maximum variation of 10% between clinical cure rates. The rate of successful treatment for the usual duration of antibiotic therapy (15 days) is between 80 and 90%.

Patients are randomized after the result of the BAL: it is estimated that 20% of patients pre-included may not be included permanently. This produces a risk equal to 0.20. The number of subjects to be included must be a minimum of 275 and maximum of 350 for the initial value of the rate of cure and the risk (chosen, as indicated in the table below):

| %  cured |  |  | n/group | N pre included | Total included |
| --- | --- | --- | --- | --- | --- |
| 0.90 | 0.05 | 0.20 | 110 | 275 | 220 |
| 0.85 | 0.10 | 0.20 | 110 | 275 | 220 |
| 0.80 | 0.10 | 0.20 | 140 | 350 | 280 |

The number of patients selected for the study is 350.

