**3. Objectives of the study**

**This is a prospective, randomized, open, multi-center study.**

**3.1 Primary Objective**

To show that antibiotic therapy of 8 or 15 days is equivalent in terms of clinical cure rates in the treatment of early onset nosocomial pulmonary infection in patients receiving mechanical ventilation.

- 1. **Secondary Objective**

**. Study of nosocomial infections:** assessing the influence of the duration of antibiotic treatment on the rate of potentially fatal pulmonary and extra-pulmonary infection (definition of nosocomial infections: annex XIII).

- **Study of bacterial Ecology:** research of changes in the flora of the gut under treatment and analysis of pathological samples (antibiotic resistance phenotypes +/- genotypes).

**. Economic Survey:** analyze the costs related to the treatment of nosocomial pneumonia and its complications in the two study groups.

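### Equivalence is claimed with no direction, but 140 per group fits a one-sided calculation: about 79% power for one direction, about 58% for both bounds at a cure rate of 0.80

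*Protocol*

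**What the plan says.** The primary objective (Protocol 3.1) is "To show that antibiotic therapy of 8 or 15 days is equivalent in terms of clinical cure rates". Section 11.1 repeats the aim: "It is a therapeutic trial of equivalence, with two parallel groups". Section 11.2 sets the margin: "the equivalence is accepted up to a maximum variation of 10% between clinical cure rates". None of these limits the claim to the short course being no worse, and no one-sided or non-inferiority aim appears elsewhere in the protocol.

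For planning, 11.2 says: "The rate of successful treatment for the usual duration of antibiotic therapy (15 days) is between 80 and 90" percent. It adds that "it is estimated that 20% of patients pre-included may not be included permanently", followed by "This produces a risk equal to 0.20". The table has three scenarios. The one adopted reads "0.80 | 0.10 | 0.20 | 140 | 350 | 280": cure rate, two unlabelled error columns, n per group, number pre-included and number included.

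The statistical analysis paragraph after 11.3 judges equivalence by a confidence interval for an odds ratio. It gives neither the confidence level nor the number of sides.

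**The concern.** A claim of equivalence within 10 points needs two bounds excluded: the short course must be neither 10 points worse nor 10 points better. That needs more patients than excluding one bound. If the table was built for one bound, the trial has less power for its written claim than the table implies, and could miss that claim fairly often even if the two durations cure equally well. If only one direction was meant, the size is about right, but the objective, design and margin describe a different claim.

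**Working it through.** **Inputs.** From 11.2: margin 0.10 on the difference in cure rates, cure rates 0.90, 0.85 and 0.80, and the two error columns. Equal allocation follows from 140 per group and 280 in total. Two inputs are assumptions: no true difference between arms, and the first error column is alpha and the second beta.

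**1. Reproduce the table.** One-sided formula: n = 2p(1−p)(z₁₋α + z₁₋β)² / 0.10².

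- p = 0.90, α = 0.05: 0.18 × (1.645 + 0.842)² / 0.01 = 111.3
- p = 0.85, α = 0.10: 0.255 × (1.282 + 0.842)² / 0.01 = 115.0
- p = 0.80, α = 0.10: 0.32 × (1.282 + 0.842)² / 0.01 = 144.3

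Each stated value is the result rounded down to a ten. The pre-inclusion step is correct: 280 / 0.80 = 350 and 220 / 0.80 = 275.

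**2. Try the alternatives.**

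| Calculation | 0.90 row | 0.85 row | 0.80 row |
| --- | --- | --- | --- |
| Stated | 110 | 110 | 140 |
| One-sided α | 111 | 115 | 144 |
| α split in two | 141 | 158 | 198 |
| Both bounds, α on each side (z₁₋β/₂ in place of z₁₋β) | 154 | 168 | 210 |

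Superiority formulas, with and without continuity correction, give 115 to 251 for the 0.80 row. Some come near a single row, but none fits the whole table. A one-sided formula with the variance taken at p ± 0.05 gives 109, 114 and 143. So the exact formula is not settled, but the direction is.

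**3. Power of the chosen row.** With 140 per group and p = 0.80, SE = √(0.32/140) = 0.0478 and 0.10/0.0478 = 2.092.

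- One direction, α = 0.10: Φ(2.092 − 1.282) = 0.791
- Both bounds, 0.10 per side: 2 × 0.791 − 1 = 0.582

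Exact binomial enumeration with Wald limits gives 79.3% and 58.6%.

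**4. Sensitivity to the cure rate** (140 per group, 0.10 per side, both bounds): 58% at 0.80, 71% at 0.85, 87% at 0.90.

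**5. Sensitivity to alpha** (140 per group, cure 0.80):

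| α per side | One direction | Both bounds |
| --- | --- | --- |
| 0.10 | 79% | 58% |
| 0.05 | 67% | 35% (formula 34.5, exact 34.9) |
| 0.025 | 55% | 11% (formula 10.5, exact 11.0) |

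**6. Scale.** A 10-point deficit is not one odds ratio. From 0.80 to 0.70 it is (0.70/0.30)/(0.80/0.20) = 0.58; from 0.90 to 0.80 it is (0.80/0.20)/(0.90/0.10) = 0.44. The powers above therefore do not carry over to an odds-ratio rule.

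**The case against.** **The error labels are inferred.** This stands as a limit. The formula is symmetric in the two error rates, so reproducing n cannot show which column is alpha. With the columns reversed (0.20 per side), two-bound power at 140 per group and cure 0.80 is 2Φ(2.092 − 0.842) − 1 = 79%, against a planned 90%. Alpha before beta is the usual order and the likelier reading. The shortfall for a two-bound claim exists either way; its size depends on the labels. The 0.20 could also be taken as the attrition fraction, since the sentence stating it follows the one on attrition. But attrition is already the step from 280 to 350, and 0.20 is also needed as an error rate to reach 140.

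**Equivalence may loosely mean not worse.** The rationale favours shorter treatment and takes 15 days as the usual duration, which suits a one-directional aim. On that reading 140 per group gives about 79%, close to 80%. The size is then sound, but the wording in 3.1, 11.1 and 11.2 is not.

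**The confidence level may be in the analysis plan.** That is possible, so a reader who takes 35% or 11% as the trial's power goes beyond the protocol: those values rest on levels it does not state.

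**Alpha differs between rows.** A reader might call this an error. It is not one in itself: the rows are planning scenarios, and only one was adopted.

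**Conclusion.** The protocol's claim and its sample size do not match. As written, the claim has two bounds; the table was sized for one. The chosen row has about 79% power for one direction and about 58% for both bounds. This rests on cure 0.80 in both arms, alpha 0.10 per side, the conventional reading of the unlabelled columns, and the risk-difference scale.

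A reader might infer that the trial flatly has 58% power instead of a stated 80%. The protocol does not support that. No sentence in it states 80% power, and 58% belongs to the bottom of the planned cure range, rising to 71% and 87% at 0.85 and 0.90. Nor is 140 a slip of arithmetic: it follows from a one-sided calculation, rounded down. The fault is that the protocol never says one-sided and words its claim the other way. It matters because, at cure 0.80 with identical arms, the written claim would be missed about four times in ten (1 − 0.58 = 0.42) even at the lenient 0.10 level.

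**What to change.** Leave N unchanged and choose one of two wordings.

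- **One direction.** Restate 3.1, 11.1 and 11.2 so that the claim is that 8 days is not worse than 15 days by 10 points or more in D21 cure. State one-sided alpha 0.10 and power of about 79%.
- **Equivalence kept.** State that both bounds must be excluded and that power is about 58% at cure 0.80 with 0.10 per side.

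In either case:

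- State one alpha with its matching confidence level: an 80% interval for 0.10 per side, 90% for 0.05, 95% for 0.025. If a stricter level is chosen, restate the power at cure 0.80 as 67% (one direction) or 35% (both bounds) at 0.05, and 55% or 11% at 0.025.
- In the statistical analysis paragraph after 11.3, judge the claim by the confidence interval for the difference in cure rates, so that the rule matches the 10-point margin and the stated power.
- Label the error columns in words and say that alpha is per side.

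The cost is protocol wording: a narrower claim or a less favourable stated power, with no extra patients. For scale only, 80% two-bound power at cure 0.80 and 0.10 per side would need 211 per group: 422 included and 422/0.80, or 528, pre-included.

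### Section 11.2 sizes the groups for a single 10-point limit, while the protocol declares undirected equivalence; power for both limits in the chosen row is about 58%, not 80%

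*Protocol*

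**What the plan says.** Three places define the claim, and none gives it a direction.

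- Section 3.1 states the primary objective: "To show that antibiotic therapy of 8 or 15 days is equivalent in terms of clinical cure rates".
- Section 11.1 states the design: "It is a therapeutic trial of equivalence, with two parallel groups".
- Section 11.2 sets the margin: "the equivalence is accepted up to a maximum variation of 10% between clinical cure rates".

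Section 11.2 also gives the reference rate: "The rate of successful treatment for the usual duration of antibiotic therapy (15 days) is between 80 and 90" percent. Its table has three rows. The headers of columns 2 and 3 cannot be read in the text at hand. The first column is the proportion cured, and the last three are n per group, number pre-included and total included:

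- "0.90 | 0.05 | 0.20 | 110 | 275 | 220"
- "0.85 | 0.10 | 0.20 | 110 | 275 | 220"
- "0.80 | 0.10 | 0.20 | 140 | 350 | 280"

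The size selected is 350, which matches the third row: 350 pre-included, 280 included, 140 per group. The statistical analysis paragraph after section 11.3 judges equivalence by a confidence interval and names an odds ratio. It gives neither level nor sidedness. Non-inferiority is not mentioned anywhere in the protocol.

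**The concern.** An equivalence claim with an undirected 10-point margin succeeds only if the lower limit of the difference is above -10 points and the upper limit is below +10 points. A non-inferiority claim needs only the first. The two need different sample sizes for the same error rates, because an equivalence trial can miss on either side.

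The table looks like a one-limit calculation. If so, its 0.20 is not the type II risk of the declared claim. A trial of two equally effective durations could then fail that claim much more often than the protocol says, even with 8 days not shown to be worse. The choice also decides what counts as success: an upper limit above +10 in favour of 8 days fails equivalence but passes non-inferiority.

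**Working it through.** **Inputs.** From section 11.2: margin d = 0.10, cure rates p of 0.90, 0.85 and 0.80, and n per group of 110, 110 and 140. Columns 2 and 3 are read as alpha (0.05, 0.10, 0.10) and beta (0.20), an inference from their order. Equal true cure rates are assumed; the protocol does not state this. Limits are taken on the risk difference, each at one-sided alpha. Normal quantiles: z(0.95) = 1.645, z(0.90) = 1.282, z(0.80) = 0.842.

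**Step 1: reproduce the printed sizes.** With one limit, n = 2p(1-p)(z(1-alpha) + z(1-beta))² / d².

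- Row 1: 2 × 0.09 × (1.645 + 0.842)² / 0.01 = 111.3; printed 110.
- Row 2: 2 × 0.1275 × (1.282 + 0.842)² / 0.01 = 115.0; printed 110.
- Row 3: 2 × 0.16 × (1.282 + 0.842)² / 0.01 = 144.3; printed 140.

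Rows 1 and 3 are within about 3% of the printed sizes. Row 2 is the loosest, about 4% off. One-limit power at the printed sizes is 79.6%, 78.7% and 79.1%, close to 80% throughout.

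**Step 2: try other formulas.**

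| Formula | Row 1 | Row 2 | Row 3 |
| --- | --- | --- | --- |
| Printed | 110 | 110 | 140 |
| One limit, full alpha | 111.3 | 115.0 | 144.3 |
| One limit, alpha/2 | 141.3 | 157.7 | 197.8 |
| Both limits, beta/2 on each side | 154.1 | 167.5 | 210.2 |

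One-limit sizing with the variance taken under the null gives 110, 114 and 143, so it is the same family. One-sided superiority (157, 144, 169), arcsine (154, 143, 168) and log odds ratio (209, 175, 194) formulas do not fit.

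**Step 3: power for both limits at the printed sizes.** With SE = √(2p(1-p)/n), power = 2Φ(d/SE - z(1-alpha)) - 1.

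For the chosen row, SE = √(0.32/140) = 0.0478 and d/SE = 2.092. Then 2.092 - 1.282 = 0.810 and Φ(0.810) = 0.791. Power for both limits is 2 × 0.791 - 1 = 0.582, so the type II risk is about 0.42.

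The same formula gives 59.2% for row 1 and 57.4% for row 2. Exact binomial enumeration with Wald limits gives 61.2%, 57.1% and 58.6% for the three rows.

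**Step 4: the selected 140 per group over the stated range of cure rates.**

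| Cure | Alpha per limit | Power, one limit | Power, both limits |
| --- | --- | --- | --- |
| 0.80 | 0.10 | 79.1% | 58.2% |
| 0.85 | 0.10 | 85.6% | 71.2% |
| 0.90 | 0.05 | 87.4% | 74.7% |
| 0.90 | 0.10 | 93.4% | 86.8% |

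**Step 5: where the misses fall.** Exact enumeration for the chosen row gives a probability of 0.207 that the lower limit fails, 0.207 that the upper limit fails, and 0 that both fail. The total is 0.414. Every miss added by the second limit is therefore an upper-limit breach, with a higher observed cure rate on 8 days.

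**The case against.** The strongest reply is that the designers meant one limit. The words two-sided and non-inferiority are both absent, a cure rate is given only for the usual 15 days, and section 10.2 presents the short course as carrying less ecological risk at equal clinical effectiveness. The table's own fit to a one-limit formula points the same way. This may well be the intent. The calculation is then sound and the wording of 3.1, 11.1 and 11.2 is what needs correcting. It does not remove the mismatch. A SAP could specify the interval, but claim, margin and size all stand in this protocol and disagree there.

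Three further points limit the finding. The 58% belongs to cure 0.80 and alpha 0.10; at cure 0.90 with alpha 0.10, 140 per group gives 87%. The check uses a risk difference, while the analysis paragraph names an odds ratio interval, so the figures describe the 10-point margin of 11.2 and not that interval. The fit is approximate in row 2. If all 350 were randomised (175 per group), power for both limits at cure 0.80 and alpha 0.10 would be 71%, but the table shows 350 as pre-included.

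Two stronger readings are tempting. A reader might infer that the extra failures would count against 8 days. They would not: step 5 shows that they all favour 8 days, and the risk of missing the lower limit is about 0.21, essentially as printed. A reader might also take "This produces a risk equal to 0.20", which follows directly on the 20% pre-inclusion loss, to mean that the risk was derived from the loss. The table keeps the two apart: 0.20 has its own column, and the loss enters as 220/0.8 = 275 and 280/0.8 = 350. The sentence is probably a translation slip or has lost a symbol.

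**Conclusion.** The concern holds as a mismatch between the declared claim and the calculation behind the group sizes. Undirected equivalence within 10 points is stated, and the sizes fit a single limit. In the chosen row, power for the declared claim is about 58% (59% by exact enumeration) instead of 80%. At 140 per group it stays below 80% for each cure rate at the alpha paired with it in the table (58%, 71% and 75%), and exceeds 80% only at cure 0.90 with alpha 0.10.

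This rests on reading the unlabelled columns as alpha and beta, on no true difference, and on risk-difference limits. The consequence is limited: the trial could fail its equivalence claim although 8 days is not shown to be worse. Protection against missing the lower limit is close to what the protocol prints.

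**What to change.** Keep 140 per group and make the claim and the figure agree, in one of two ways.

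1. State the primary hypothesis in 3.1, 11.1 and 11.2 as one-sided non-inferiority of 8 versus 15 days: the lower limit for cure at 8 days minus cure at 15 days lies above -10 points, at one-sided alpha 0.10. The existing size then has about 79% power at cure 0.80.
2. Keep equivalence, say that both limits must lie within 10 points, and restate the power at 140 per group as about 58% at cure 0.80 and 71% at 0.85 (alpha 0.10), and at 0.90 as 75% (alpha 0.05) or 87% (alpha 0.10).

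Either way, label the table's risk columns and say whether they refer to one limit or both.

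The cost is wording in the protocol and, if one exists, the SAP. No patients are added and the margin is unchanged. The second option means printing a less favourable power. Keeping equivalence at 80% power instead would need about 211 per group in the chosen row: 422 included and, at 422/0.8, about 528 pre-included. That is not needed to resolve the mismatch.

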**11.3 Study duration**

With the recruitment of investigators centres, we estimate the total number of patients included per year to be 120. Therefore, a total study duration of 3 years is estimated in order to recruit the required number of patients who will additionally be followed for 21 days. Every 4 months, a balance sheet of the inclusions will be sent to all investigators centres. To be accepted in the final analysis, each centre must recruit at least 6 patients.

- 1. **Statistical analysis**
- Patients excluded from the analysis include those whose bacteriological samples collected during pre-inlusion do not respond to the criteria laid down.
- Analysis: Non-excluded patients will be analysed by the treatment defined by the drawing of lots (intention to treat). Comparatability of the 2 groups will be performed on the main characteristics and prognostic factors with traditional tests: test t Student for quantitative variables and test of Chi 2 qualitative variables. For the main criterion, the equivalence will be judged by the confidence interval of the odds ratio of the percentage risk (test of decentralized Chi 2).

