**8.3 Randomisation**

Is carried out in the final inclusion. It will be performed by the main investigator centre using a pre-defined centre randomization table. The assigned treatment arm is communicated by fax between 8 a.m. and 12 p.m., Monday to Friday and at the latest by D5.

1. **Methodology**

- **Pre-inclusion**
- verification of the criteria for inclusion (except bacteriological data) and exclusion
- realization of the BAL
- realization of 3 blood cultures
- simplified acute physiologic score: SAPSIIS II (Appendix VIII)(Appendix IX) Mc Cabbe score - score of organ failure (ODIN: Appendix X)
- -score of organ failure related to sepsis (SOFA: Appendix V)
- **Inclusion**
- verification of the bacteriological criteria for inclusion.
- **D0 of treatment**
- SAPS II (Appendix VIII) score
- score of organ failure (ODIN: Appendix X)
- score of organ failure related to sepsis (SOFA: Appendix V)
- **D1 of treatment**
- SAPS II (Appendix VIII) score
- score of organ failure (ODIN: Appendix X)
- score of organl failure related to sepsis (SOFA: Appendix V)
- rectal swabs
- **D4 of treatment**
- **decrease of dosages of beta-lactam - interim evaluation**

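### The six-patient centre rule removes randomised patients, so the set labelled intention to treat is not all randomised patients, and the sample size has no reserve for the loss

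*Protocol*

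**What the plan says.** The rule stands at the end of Protocol section 11.3 (Study duration), after the recruitment forecast and the four-monthly inclusion reports: "To be accepted in the final analysis, each centre must recruit at least 6 patients".

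The statistical analysis list that follows defines the analysed patients in two steps. First, an exclusion: "Patients excluded from the analysis include those whose bacteriological samples collected during pre-inlusion do not respond to the criteria laid down". Then the allocation principle: "Non-excluded patients will be analysed by the treatment defined by the drawing of lots (intention to treat").

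Section 11.2 fixes the order of events: "Patients are randomized after the result of the BAL". It also gives the design inputs: "the equivalence is accepted up to a maximum variation of 10% between clinical cure rates", and "The rate of successful treatment for the usual duration of antibiotic therapy (15 days) is between 80 and 90" percent. The table row that leads to the chosen number of 350 reads "0.80 | 0.10 | 0.20 | 140 | 350 | 280". The only loss it allows for is 20% of pre-included patients who are not finally included.

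**The concern.** The two kinds of exclusion differ in timing. A BAL that misses the threshold is known before the patient is randomised, so leaving that patient out takes nothing from the randomised comparison. A centre's final count is known only when it has finished recruiting. By then its patients have been randomised and treated, and most or all have been assessed. Dropping them is an exclusion after randomisation, and it is decided by how many other patients the centre happened to enrol.

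Two things are at stake. First, the primary analysis set would be called intention to treat without containing everyone randomised. Secondly, the trial would lose patients it has already paid for, against a sample size that makes no provision for losing them.

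**Working it through.** **1. Order of events.** By sections 8.2, 8.3 and 11.2, a patient is pre-included, has the BAL result read, is finally included and is then randomised. The BAL exclusion acts before randomisation. The centre rule can act only after it.

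**2. Inputs.** All come from section 11.2: margin 0.10, cure rate 0.80 to 0.90, and 140 per group in the 0.80 row. The headings of the second and third table columns are blank in the text at hand. I read them as alpha and beta.

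**3. Reproducing the plan's table.** The one-sided formula for equal true cure rates *p* is

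n per group = 2p(1−p)(z₁₋α + z₀.₈₀)² / 0.10²

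| Cure | Alpha | Formula | Plan | Power at the plan's n |
|---|---|---|---|---|
| 0.90 | 0.05 | 112 | 110 | 79.6% |
| 0.85 | 0.10 | 115 | 110 | 78.7% |
| 0.80 | 0.10 | 145 | 140 | 79.1% |

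For the last row: 0.32 × (1.282 + 0.842)² / 0.01 = 144.3, rounded up to 145. Taking the null variance at p ± 0.05 gives 110, 114 and 143. Halving alpha gives 142, 158 and 198, which does not fit. The table therefore follows a one-sided calculation, with small differences.

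**4. Reserve.** 280 / (1 − 0.20) = 350 and 220 / (1 − 0.20) = 275, both exact. Run forwards, 350 × 0.80 = 280, which is the number the 0.80 row requires. Nothing is left over for patients of rejected centres.

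**5. Power if patients are dropped.** With *m* patients analysed per group,

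power = Φ(0.10 / √(2p(1−p)/m) − z₁₋α)

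At p = 0.80, alpha 0.10 and m = 140: √(0.32/140) = 0.0478, 0.10/0.0478 = 2.092, and 2.092 − 1.282 = 0.810, so power is 79.1%.

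The documents give neither the number of centres nor the recruits per centre, so the patients lost are an assumption. A rejected centre holds at most 5 randomised patients, so the fewest failing centres is the loss divided by 5.

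| Patients lost (assumed) | Fewest failing centres | Analysed | Power |
|---|---|---|---|
| 0 | 0 | 280 | 79.1% |
| 20 | 4 | 260 | 76.9% |
| 40 | 8 | 240 | 74.4% |
| 60 | 12 | 220 | 71.7% |

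**6. The favourable end.** At cure 0.90 and alpha 0.05, 280 patients give 87.4%. After a 20% loss (224 patients, 112 per group), √(0.18/112) = 0.0401, 0.10/0.0401 = 2.494, and 2.494 − 1.645 = 0.850, so power is 80.2%. At that cure rate the rule costs precision but does not take power below 80%.

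**The case against.** The strongest reply is that the Protocol does not promise to analyse everyone randomised. It applies intention to treat to non-excluded patients, and its list of exclusions is open-ended. A reader might infer that two sentences flatly contradict each other. The wording does not go that far, since the centre rule can be read as one more exclusion applied first. That reply stands as to wording. It does not rescue the label, because what remains is still not the full randomised set.

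A reader might also infer bias: in an open trial, a centre could stop at five because of what it has seen. The documents do not show this. The rule is set in advance, takes whole centres and ignores arm. A rejected centre has at most five patients over both arms, and the four-monthly reports cover inclusions, not outcomes. Such selection remains possible and no more.

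On size, the loss may be nil, and large losses need many failing centres. A reader who required both equivalence bounds to be met would find much lower power. Most of that gap comes from the one-sided sample-size method, is present before any centre is dropped, and should not be charged to this rule.

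Finally, the phrase "using a pre-defined centre randomization table" in section 8.3 might suggest that randomisation is stratified by centre and that the analysis wrongly ignores it. The phrase may equally mean a table held at the coordinating centre. Adjustment for centre is also a detail that an SAP may settle.

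**Conclusion.** The point holds in a limited form. As written, the rule removes patients after randomisation, is not reconciled with the intention-to-treat label, and has no allowance in the sample size. This follows from the text and needs no assumption about centres.

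The power cost does need one. It is about 2, 5 or 7 percentage points if 20, 40 or 60 of the 280 patients sit in small centres, at cure 0.80 and one-sided alpha 0.10. It is zero if every centre reaches six, and it leaves power near 80% at cure 0.90 and alpha 0.05 even after a 20% loss. These figures rest on a normal approximation, equal true cure rates, equal loss in both arms, and alpha and beta as the missing column headings. Biased selection of centres is a possibility that the rule leaves open, not a finding. The Protocol gives no reason for the threshold, so its purpose cannot be judged.

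**What to change.** Delete the sentence, or confine it to site management or authorship. State that the primary analysis includes every randomised patient with a qualifying BAL, from every centre, in the arm drawn by lot. If centre is used in the analysis, pool the small centres. A set restricted to centres with at least six patients may be kept as a sensitivity analysis; in that case, say whether the six are counted as pre-included or as randomised.

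The cost is a change of wording, plus one extra run if the sensitivity analysis is kept. No further patients or data are needed.

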**5.5** **Antibiotic adjustment**

If a new pulmonary or non pulmonary superinfection develops, all antibiotics are usable, supported by bacteriological data. Any change of antibiotic treatment for new pulmonary infection occurring after the beginning of the protocol has to be supported by a BAL if the patient is intubated.

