**7.3 Intercurrent pulmonary infectious events**

Any intercurrent infectious event is documented by a new BAL. If a different bacteria is present at significant concentration, the patient is considered superinfected and is still evaluable at D21 ; if the BAL is sterile, treatment is continued and the patient will be evaluate at D21

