**7.4 Non-pulmonary infectious intercurrents events**

Any modification of antibiotics will be preceded by the collection of bacteriological samples deemed necessary. If an intercurrent non-pulmonary Infection is documented, the patient is considered superinfected and remains evaluable at D21 on intention to treat.

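### Equivalence rests on intention to treat with no supporting analysis, although permitted further antibiotics can bring the two treatment durations together and favour the claim

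*Protocol*

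**What the plan says.** Section 11.1 sets out the aim and the endpoint: "It is a therapeutic trial of equivalence, with two parallel groups of which the main criterion is the rate of clinical cure at the end"; the assessment falls on D21. Section 11.2 gives the margin: "the equivalence is accepted up to a maximum variation of 10% between clinical cure rates". Section 3 describes the trial as open.

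The statistical analysis paragraph that follows section 11.3 states: "Non-excluded patients will be analysed by the treatment defined by the drawing of lots (intention to treat"). It then judges equivalence by a confidence interval. It names no other analysis set and no condition that a second analysis should agree.

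The randomised contrast, in section 5.2, is the day on which the beta-lactam stops: J9 in the short arm, J16 in the long arm. Three other places bear on whether that contrast is preserved:

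- Section 5.5: "If a new pulmonary or non pulmonary superinfection develops, all antibiotics are usable", provided bacteriological data support it. A BAL is also required when treatment is changed for a new lung infection in an intubated patient. No limit on duration is given.
- Section 7.3: a patient whose new BAL grows a different organism at a significant count is superinfected and still evaluable at D21. It adds: "if the BAL is sterile, treatment is continued and the patient will be evaluate at D21".
- Section 7.4: with a documented non-pulmonary infection, "the patient is considered superinfected and remains evaluable at D21 on intention to treat".

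Section 7.2.2 also drops temperature and leukocytes from the cure criteria when an extra-pulmonary infection is documented.

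**The concern.** Under these rules a short-arm patient can receive antibiotics through J9 to J16 for a documented superinfection and still be counted as a short-arm cure. In a superiority trial, such convergence of actual treatment works against the claim. In an equivalence trial it works in favour of it: the observed difference shrinks and the interval fits more easily inside the margin. Because the trial is open, clinicians also know who is due to stop at J9.

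The trial's single main conclusion is at stake. An intention-to-treat result within the margin could mean that 8 days does as well as 15, or that the courses actually received differed less than planned. The protocol plans no analysis to tell these apart.

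**Working it through.** **Inputs from section 11.2.** Margin 0.10 on the cure rates. Long-arm cure: "The rate of successful treatment for the usual duration of antibiotic therapy (15 days) is between 80 and 90"%. The row behind the chosen size reads "0.80 | 0.10 | 0.20 | 140 | 350 | 280". Its second and third column headings did not survive text extraction, so I read 0.10 as alpha and 0.20 as beta. Sidedness is not stated.

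**Reproducing the plan's sizes.** One-sided formula with equal true rates p: n per group = 2p(1−p)(z₁₋α + z₀.₈₀)² / 0.10².

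| p | alpha | computed n | stated n | one-sided power at stated n |
|---|---|---|---|---|
| 0.90 | 0.05 | 111.3, so 112 | 110 | 0.796 |
| 0.85 | 0.10 | 114.95, so 115 | 110 | 0.787 |
| 0.80 | 0.10 | 144.3, so 145 | 140 | 0.791 |

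The stated sizes fit this formula rounded down to a multiple of ten. The pre-inclusion totals are exact: 220/0.8 = 275 and 280/0.8 = 350. The 20% allowance covers losses before randomisation; nothing is allowed for deviations after it.

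**Effect of convergence.** Let the true short-course deficit equal the margin. Assume that a share c of the short arm receives enough further antibiotic to reach the long-arm cure rate pL. The protocol gives no value for c.

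- Short-arm cure: pS = pL − 0.10(1−c)
- SE = √[pL(1−pL)/n + pS(1−pS)/n]
- One-sided chance of concluding equivalence = Φ((0.10 − (pL − pS))/SE − z₁₋α)
- For both bounds, subtract Φ((−0.10 − (pL − pS))/SE + z₁₋α)

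Worked case (pL = 0.80, n = 140, alpha 0.10, c = 0.20): pS = 0.72; SE = √(0.16/140 + 0.2016/140) = 0.0508; (0.10 − 0.08)/0.0508 = 0.394; 0.394 − 1.282 = −0.888; Φ = 0.187.

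| c | 0.80 / 0.10 / 140: one-sided | both bounds | 0.90 / 0.05 / 110: one-sided | both bounds |
|---|---|---|---|---|
| 0 | 0.100 | 0.095 | 0.050 | 0.045 |
| 10% | 0.139 | 0.131 | 0.076 | 0.068 |
| 20% | 0.187 | 0.175 | 0.112 | 0.099 |
| 30% | 0.246 | 0.227 | 0.161 | 0.141 |

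About 20% convergence roughly doubles the error rate.

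**Power in a smaller per-protocol set** (p = 0.80, alpha 0.10, one-sided). If 10%, 20% or 30% of patients leave the set, n per group falls from 140 to 126, 112 or 98. Power falls from 0.791 to 0.759, 0.722 or 0.680.

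**The case against.** Intention to treat is a legitimate answer to the question of whether to prescribe 8 or 15 days, and an unseen SAP could add a supportive analysis. Both points stand. They are why intention to treat should remain the deciding analysis. They do not remove the point, because the protocol itself names the set on which equivalence is decided and attaches nothing to it.

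The protocol has guards. Further antibiotics need bacteriological support (5.5), so agent and duration are unrestricted but the trigger is not. Death, persistent signs with the original organism, worsening with the same organism on a new BAL, and a change for intolerance are failures that stand at D21 (7.2.1). For patients at home, a new antibiotic for a lung infection rules out cure (7.2.2). These guards catch much of the case where an inadequate short course is rescued by more antibiotic. They do not cover a hospital patient treated for a different organism or at another site.

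The model is generous to the concern. It gives every extra-treated patient the full long-arm cure rate, although such patients have a second infection and may do worse. It also works on the difference in rates, whereas the protocol refers to an odds-ratio interval.

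A reader might infer that the sterile-BAL sentence in 7.3 is another route to longer short-arm treatment. The text does not support that: it can be read as leaving the assigned course unchanged, and nothing in it extends the J9 stop in 5.2.

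A reader might also want equivalence to require success in a set defined by actual antibiotic days. That set would lose superinfected patients mainly from the short arm, since antibiotics between J9 and J16 break the short course but need not break the long one. As an assumed illustration, let 20% of the short arm be superinfected with 50% cure and the rest have 75%. True cure is 0.2 × 50% + 0.8 × 75% = 70%, but the selected set shows 75%, which halves a 10-point deficit against 80%. This objection is sound and shapes the fix.

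**Conclusion.** The point holds in a limited form. The protocol decides equivalence on the as-randomised set with no supporting analysis, in an open trial that allows further antibiotics of unlimited duration in evaluable patients. Any resulting convergence favours the claim.

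The direction is clear; the size is not. The tabulated error rates rest on an assumed share, a true deficit equal to the margin, full long-arm benefit in every extra-treated patient, a normal approximation, and alpha and beta as inferred from the table. They are upper-end illustrations for each share, not forecasts. The documents do not show that many short-arm patients will be over-treated, that intention to treat is the wrong deciding set, or that a second analysis must also succeed before equivalence is claimed.

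**What to change.** In the statistical analysis paragraph of section 11:

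1. Keep intention to treat as the deciding analysis.
2. Add a pre-specified supportive per-protocol analysis of the main criterion. It excludes eligible patients whose assigned course was lengthened or shortened without a documented reason that the protocol allows. It keeps deaths and section 7.2.1 failures as failures, and does not drop patients merely for a documented superinfection.
3. Report total antibiotic days to D21 by arm.
4. State that equivalence will not be presented as robust if the two analyses disagree.

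Separately, sections 7.3 and 5.2 should be reconciled on what continuing treatment means after J9.

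The cost is modest. The daily follow-up sheet (Appendix VII) already records antibiotics, and the economic study (10.3) already counts days under anti-infective treatment. The downside should be stated in the protocol: the per-protocol set is smaller, with the reduced power shown above, and is not protected by randomisation. Because it is supportive and not co-primary, the planned 350 need not change.
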